### Participants

Informed written consent was provided by all participants prior to baseline assessments. A copy of a plain English statement describing the research project is held by participants. The consent form includes information about withdrawal of consent and that withdrawal from the research project will not affect their status now or in the future.

### Inclusion criteria

1. Aged 18 - 64 years at recruitment;

2. Identify as Aboriginal and/or Torres Strait Islander;

3. Waist circumference > 80.0 cm at baseline assessment.

### Exclusion criteria

1. Pregnant at baseline assessment or if they become pregnant during the study period;

2. Physically unable to participate in the program based on medical advice from their treating doctor.

### Recruitment

Participants were recruited in three intakes (April 2010, September 2010 and March 2011). The first two programs were delivered at the City East Campus of the University of South Australia, Adelaide. The third program was based in an outer suburb (30 km from the Adelaide CBD) with a high proportion of Aboriginal residents.

Project staff visited local Aboriginal and Torres Strait Islander organisations, health centres and community groups to inform them of the project and ask them to display posters and distribute brochures. Several information sessions were held during each recruitment phase to allow potential participants to meet project staff and become fully informed on the project before formally registering to participate. A project flier distributed via e-mail proved to be an effective way of recruiting participants. In addition social networks were also an effective recruitment tool.

### Ethics

The study was approved by the University of South Australia's Human Research Ethics Committee and the Aboriginal Health Council of South Australia's Human Research Ethics Committee.

### Local Advisory Committee

The project is guided by an advisory committee. The committee was purposively formed for the project and is made up of local Aboriginal and Torres Strait Islander women. Some of members are representatives from the collaborating organisation Nunkuwarrin Yunti of South Australia Inc. The committee provides advice on feasibility of the project's procedures and assessments ensuring that all aspects of the project are culturally appropriate. The committee assisted in the adaptation of some surveys, gave advice on the questionnaires and will be invited to provide input into the interpretation of qualitative data.

### Staff

Staffing consists of three chief investigators, an associate investigator, and a Torres Strait Islander and Doctor of Philosophy candidate (KC). The project also employs a project coordinator, qualified fitness instructors, anthropometric assessors (ISAK accredited), a dietician and an experienced Aboriginal interviewer. All staff involved in delivering the project are female, which is essential to ensure cultural safety and sensitivity for our participants.

### Analysing the environmental determinants of obesity

The original project plan included an analysis of environmental determinant of obesity using a framework known as ANGELO (Analysis Grid for Environments Linked to Obesity). ANGELO is a process in which community members and key stakeholders attend workshops to indentify barriers to physical activity and healthy eating then formulate strategies to address the identified barriers. Prior to participants being recruited for this project, the Advisory Committee did a half day workshop to trial this framework. It was found not to be a useful tool in this setting within in the scope of the project.

### Program

The WFP is a structured 12-week physical activity group program with nutritional advice. The program consists of four key components.

1) 12 weeks of structured group exercise classes.

Each 45 - 60 minute exercise class includes a combination of aerobic and resistance training. Classes progressively increase in difficulty and intensity as the participants' fitness, strength and confidence increase. The program aims to have participants exercise at moderate to high intensity for at least 30 minutes per session. Exercises are graded according to level of difficulty to enable and challenge participants of all ability levels. Classes are coordinated and supervised by project staff and delivered by qualified instructors. The exercise classes are implemented as outlined in the 'Program Manual'. The Program Manual provides the instructors and staff with a set of guidelines and resources for implementing each exercise session.

2) Incidental activity and walking.

Participants are encouraged to reach 10,000 steps daily or 70,000 weekly. Pedometer readings are self-recorded in their 12-week exercise diaries. Staff document the recorded steps when the participants bring their exercise diaries to group sessions. The exercise diaries are also collected at the end of the program.

3) Nutrition Workshops

Four nutrition workshops led by a qualified dietician are conducted during the 12-week program. Topics include basic nutrition, food label reading, recipe modification and healthy takeaways options. The workshops highlight practical changes that the women can incorporate into their daily lives. Workshop content was adapted from the Whyalla Nutrition and Exercise Study [25] with permission from the principal researcher and author. The final workshop is an interactive cooking demonstration involving participants making three tasty, nutritious dishes.

4) Positive reinforcement and encouragement

Fortnightly newsletters are distributed to participants during the 12-week program. Each newsletter contains a healthy recipe, tips on nutrition and physical activity and acknowledges the participants who have logged the most steps for the fortnight. The project staff provide regular participant feedback on the quality of their exercise technique and their progress, as well as encouragement to wear their pedometer and record their daily steps.

The group exercise classes and nutrition workshops aim to bring together 'like minded' Aboriginal and Torres Strait Islander women facing similar barriers to living a healthy lifestyle, that harbours social support and creates a culturally 'safe' environment.

Waitlisted participants they also receive a pedometer, exercise diary. They also are posted monthly newsletters and are invited to attend workshops over the 12 month waiting period. The waitlisted participants are invited to suggest topics for these workshops. Some workshops that have been delivered based on participant requests include "Fad diets - myths and facts", "Healthy Recipes" and "How to stay healthy over Christmas".

### Program logic model

Figure 1 shows an abridged version of the program logic model. The model depicts the anticipated change process through women's participation in the program. The 12-week WFP hopes to activate positive psychosocial (i.e. perceived self-efficacy, motivation and perceived social support) and behavioural changes (an increase in moderate and vigorous physical activity, reduced sedentary activity, reduced saturated fat intake, reduced sweetened drinks, increase in dietary fibre, fruit and vegetables intake) in the participants. These results should lead to intermediate outcomes of reduced WC and improved metabolic health. Long-term outcomes are beyond the scope of the research project however long-term follow up studies such as the Finnish Diabetes Prevention Program and Da Qing in China suggest that their participants had a reduction in the incidence of lifestyle chronic diseases for several years post program [26,27]. If the Aboriginal and Torres Strait Islander Women's Fitness Program produces results similar to the above mentioned studies, then it could be extrapolated that this would lead to a reduction in morbidity and mortality.

**Figure 1 F1:**
[figure not shown]
**Program logic model**. This abridged version of the program logic model depicts the predicted short-term, intermediate and long-term outcomes of the program.

### Outcome Measures

Once a participant's registration form and consent is received their clinical and anthropometric assessments are taken. Participants are then given surveys to complete and a pathology request form for a fasting blood sample to be taken at their convenience. Written approval from a registered medical practitioner is required if a participant identifies a previous diagnoses of diabetes, hypertension, hyperlipidia, a heart condition, kidney disease or any other condition for which exercise may be contraindicated such as cancer. Participant requiring a medical clearance are given a letter to take to their GP which has a brief explanation of the program and an attachment for them to return. All participants have to option of requesting that their pathology results be forwarded to their GP for their medical record.

Assessments are taken at baseline, 12, 24 and 52 weeks. Waitlisted participants are invited to participate in the same assessments at the same time as the active group, with additional follow up after they participate in the 12-week program. The program timeline (Figure 2) depicts the assessment time points for both groups.

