### Study design & setting

The effectiveness of the WFP on the WC and metabolic profiles of Aboriginal and Torres Strait Islander women is being assessed using a pragmatic randomised controlled trial. The BMJ 'Clinical Evidence Glossary' defines a pragmatic study as 'an RCT designed to provide results that are directly applicable to normal practice...'[21]. There are many characteristics of a pragmatic RCT that differ from a clinical RCT such as lack of blinding, it may not employ placebos and it may focus on groups with a wide range of diagnoses [22]. The CONSORT guidelines [23] and the recommendations for pragmatic trials have been considered in the projects' design and methodology [24].

It is important that the study maintain methodological rigour whilst being culturally appropriate and ensuring that participants find the protocol acceptable. It was determined by the research team and the local Advisory committee that using traditional 'control groups' would not be acceptable. It was therefore decided that eligible participants would be randomly assigned to either the 'active' group who start the WFP immediately after their baseline assessment or to the 'waitlisted' group, who act as a comparison group for 12 months before 'crossing over' to participate in the program. Each wave of participants was randomised using the PEPI randomisation procedure to create two groups of equal size.

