### Surveys

Participants are asked to complete psychosocial and self-report behaviour surveys in their own time. The following surveys are conducted at each assessment time point i.e. baseline, 12 weeks, 24 weeks and 52 weeks.

a. Current physical activity is assessed using the Sallis seven-day physical activity recall survey [30], modified to include time spent watching television.

b. The Victorian Cancer Council Food Frequency survey (DQESv2) is used to assess the participant's dietary intake [31] and fluid intake is assessed using an instrument designed for the program.

c. The SF-36 survey is used to assess perceived quality of life [32].

d. Perceived social support for physical activity is assessed using the 'Social Support and Exercise measure developed by Sallis et al [33]. This 12-item measure assesses perceived social support by friends and family separately. Each item is scored on a 5-point Likert scale. The measure has a Cronbach alpha range of 0.60-0.91 [34].

e. Perceived self-efficacy for physical activity is assessed using a measure developed by Sallis et al. This 12-item measure assesses two sub-dimensions: a) sticking to it; and b) making time for exercise. Each item is scored on a 5-point Likert scale [35]. The measure has a Cronbach alpha range of 0.83-0.85 [36].

f. The 'Motives for Physical Activities Measure' developed by Fredrick and Ryan REF assesses the strength of five motives for participating in physical activities: 1) interest/enjoyment 2) competence 3) appearance 4) fitness and 5) social. Each item is scored on a 5-point Likert scale. The measure has a Cronbach alpha range of 0.78-0.92 [37].

Each participant receives the results of selected assessments in personalised written form. This report includes anthropometric and pathology assessments and a summary of their 7 day physical activity survey and comments from the chief investigator/project GP. Participants can also opt to have a copy of their pathology results forwarded to their treating doctor.

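### The baseline blood sample and surveys have no deadline before allocation or the first class, so their T1 values can already carry effects of allocation or the program

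*Protocol article*

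**What the plan says.** Four sections of the protocol article bear on when baseline values are obtained.

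- **Outcome Measures, staff-taken measures.** "Once a participant's registration form and consent is received their clinical and anthropometric assessments are taken".
- **Outcome Measures, blood and surveys.** The next sentence reads: "Participants are then given surveys to complete and a pathology request form for a fasting blood sample to be taken at their convenience". The blood is drawn after a fast by outside pathology services, so not at the study visit.
- **Surveys.** "Participants are asked to complete psychosocial and self-report behaviour surveys in their own time", and "The following surveys are conducted at each assessment time point i.e. baseline, 12 weeks, 24 weeks and 52 weeks".
- **Study design & setting.** The active group are those "who start the WFP immediately after their baseline assessment". On randomisation: "Each wave of participants was randomised using the PEPI randomisation procedure to create two groups of equal size". The same section names lack of blinding as a feature of pragmatic trials.
- **Statistical Analysis.** Clinical assessments are handled like waist circumference: change from T1 compared between groups, crude and adjusted for the T1 value. Psychological and behavioural variables enter regressions on waist reduction.

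**The concern.** A baseline value is useful in a randomised comparison because neither allocation nor treatment can have influenced it. Here the measures taken by staff have that property by construction. The blood sample and surveys do not: their timing is left to the participant, while one arm starts the program straight away and both arms know their allocation.

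If an active participant goes to the pathology service after classes have started, her T1 glucose, insulin, HOMA, HbA1c, lipids and CRP already contain some of whatever the program does. The change from T1 is then too small. If she fills in the motivation, self-efficacy or social support questionnaires knowing her group, that knowledge can shift her answers before any class takes place.

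At stake are the between-group comparisons of the metabolic profile, which is a stated additional aim, and the use of the self-report measures to explain waist reduction.

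**Working it through.** **1. Is there a deadline anywhere?** Set side by side, the sections give this order: registration and consent; staff measurements; surveys and blood request handed over; randomisation by wave; active group starts. The return of surveys and the blood draw have no fixed place in that order. No section ties either to randomisation, to disclosure of allocation or to the first class.

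**2. Which outcomes are exposed?**
- Waist circumference: no. The inclusion criterion is "Waist circumference > 80.0 cm at baseline assessment", staff take the measurement, and only eligible women are randomised, so it precedes allocation.
- Weight and blood pressure: no, since staff take them at the same assessment.
- Blood markers, and HOMA, which is calculated from two of them: yes.
- Self-report surveys: yes.

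The sample-size calculation rests on waist circumference. It reproduces (difference 4 cm, SD 3.47 cm, two-sided 0.05: 13 per group, power 80.5% by the noncentral t) and plays no part in this point.

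**3. Effect on blood-marker comparisons.** Let d be the true between-group difference in 12-week change, and L the share of the change already present when a late T1 sample is taken. Assume, since the article gives nothing on this, that change builds up linearly over 12 weeks. Then L = weeks late / 12:

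| Weeks after first class | L |
|---|---|
| 1 | 1/12 = 8% |
| 2 | 2/12 = 17% |
| 4 | 4/12 = 33% |

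If every T1 sample were late by the same amount:
- crude change from T1 estimates d − Ld = d(1 − L);
- analysis of covariance estimates d − b(Ld) = d(1 − bL), where b is the within-group slope of follow-up on baseline.

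For 0 < b < 1 the adjusted estimate loses less. With L = 1/3 and b = 0.6 (assumed), the crude analysis loses 33% and the adjusted one 0.6 × 33% = 20%.

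If only a fraction f of women are late, the crude loss is fL. With f = 20% (assumed) and a delay of 2 weeks, it is 0.20 × 17% = 3.3%. The documents give neither f nor the delay.

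**4. Does exposure in the waitlisted arm cancel this?** Waitlisted women receive a pedometer, diary, newsletters and workshops, so their late samples may carry some change too. If both arms are equally late, with true changes c1 and c0, the estimated difference is c1(1 − L) − c0(1 − L) = d(1 − L). The proportional loss is the same, so it does not cancel.

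**5. Surveys.** Linear build-up is not the right picture here. Physical activity is measured by a seven-day recall, so a form completed one week after classes begin describes a program week entirely. For motivation, self-efficacy and social support, answers given after allocation could move either way.

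**The case against.** The best defence is that the article's wording already orders events. Venous blood is listed under clinical assessments, surveys are placed at baseline, and the program follows the baseline assessment, so both might be read as complete before it starts. On that reading, leaving the time to the participant only reflects that she must visit an outside service fasting. This is a possible reading, but the text does not secure it: the request form is handed over after the staff measurements, with no limit on when it is used. Even on this reading, nothing excludes completion after allocation is known.

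A second defence is that an article may leave visit windows to the full protocol, and the timeline figure is not shown. That disposes of any complaint about missing windows around the 12-, 24- and 52-week assessments. It does not dispose of the baseline point, because the article states an open-ended rule rather than staying silent.

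Third, the gap between each woman's assessment and her wave's first class is unknown and may be long enough for most samples to arrive in time. That is fair, and it limits the claim to what the procedure permits.

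Fourth, a reader might infer that adjusting for a contaminated baseline makes matters worse. Against the crude change score the article also plans, it does not: for any slope between 0 and 1, adjustment loses less.

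**Conclusion.** The point holds as a defect in procedure affecting secondary outcomes. As written, T1 blood values and survey responses can be obtained after allocation is known or after classes begin. For blood markers the likely consequence is a smaller between-group difference in change from T1, only partly relieved by baseline adjustment. For surveys the direction cannot be stated.

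The size cannot be derived. The 17% and 33% are losses for an individual woman 2 or 4 weeks late under assumed linear build-up; the group-level loss scales with the unknown proportion who are late.

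Three stronger conclusions might be drawn, and the documents support none of them:
- That the primary result is compromised. Waist circumference is measured by staff and decides eligibility before randomisation.
- That late baselines occurred. The text shows only that they are allowed.
- That between-group effects on all behavioural and psychosocial measures are biased toward no difference. The article specifies no between-group analysis of the surveys; it names them as possible correlates of waist reduction.

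**What to change.** **Procedure.** State that the baseline fasting sample and surveys must be completed before allocation is disclosed, and at the latest before the wave's first class. Apply the same rule to the pre-program values of waitlisted women before they cross over, since they re-enter the data as program participants.

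**Intakes already enrolled.** The Recruitment section reports all three intakes in the past tense, so for them the remedy lies in the analysis:
- Compare each collection date with the dates of allocation and first class, and report the counts by arm.
- Use one calendar cut-off per wave, the date of its first class, in both arms. A cut-off at each woman's own first class would fall almost only on the active arm, because waitlisted women wait 12 months.
- Do not treat later values as T1. Set them to missing at baseline in a mixed model that keeps the follow-up values; the article already plans linear mixed modelling.
- Add a sensitivity analysis that includes the late values.

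**Cost.** One sentence of procedure and a date check. The downside is that some baseline values become missing, how many is unknown, and the numbers may still differ between arms. With 40 per group and nearly 60% expected loss, about 40 × 0.4 = 16 per group would have follow-up, so the model should retain every follow-up value.

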**Figure 2 F2:**
[figure not shown]
**Program timeline**. The program timeline is a depiction of the assessment time points (T1-T7) and the 12-week WFP for both the active and waitlisted groups.

Anthropometric assessments are taken by staff accredited by the International Society for the Advancement of Kinanthropometry (ISAK) using the International Standards for Anthropometric Assessment procedures [28]. ISAK assessors have an intra-tester technical error of less than 1.5% and an inter-tester reliability error of less than 2%.

i) Blood pressure and anthropometric assessments:

a. Blood pressure is measured using an Ormon T8 with an upper arm cuff after the participant has been seated for a minimum of 5 minutes. Three readings are taken and the mean of the second and third readings is also recorded.

b. Height is measured using a portable stadiometer (Leicester). The stretched stature is assessed twice to the nearest 0.1 cm; both measures and the average are recorded.

c. Weight is measured using portable digital scales (Tanita BC-532). Participants are asked to empty pockets and remove footwear and weighed wearing light clothing. Two measures and are taken to the nearest 0.1 kg. Both measurements and the average are recorded.

d. Waist and hip circumference are measured over light clothing to the nearest 0.1 cm using a flexible steel measuring tape (Lufkin w606 pm). Both measures and the average are recorded.

ii) Clinical assessments:

Venous blood samples are collected following a minimum 8 hour fast by accredited pathology services in the Adelaide metropolitan area. Pathology results are reported back to participants using the Health Scope Pathology Biochemistry Departments reference ranges [29].

a. Fasting blood glucose is analysed using Hexokinase assay with Siemens Advia 2400.

b. Fasting serum insulin is analysed using Chemiluminescent Immunoassay with Siemens Advia 2400.

c. HbA1C is analysed using Immunoturbidimetry assay with Roche Integra 800.

d. Total cholesterol, high-density lipoprotein (HDL), low-density lipoprotein (LDL) and triglycerides were analysed using Chemiluminescent Immunoassay with Siemens Advia 2400. LDL/HDL and Cholesterol/HDL ratios are also calculated.

e. C-reactive protein (CRP) is analysed using Immunoturbidimetry assay with Siemens Advia 2400.

f. Homeostatic Model Assessment (HOMA) is calculated using the formula;

$$\text{HOMA }=\;\left(\text{fasting glucose }\left[\text{mmol}∕\text{L}\right]\;\times \text{ fasting insulin }\left[\mu \text{U}∕\text{mL}\right]\right)∕\text{22}.\text{5}.$$

